### Procedures and techniques

The procedures will be done by the research team. The physical exams will be performed by an obstetrics nurse or obstetrics medical doctor that will participate in the group during all attending period. While a woman is in physical exam, the others will take turns with the responsibility of evaluate and write their own weight and blood pressure (using digital device confirmed by the medical team). After the physical exam, the women will be able to make questions and participate in the group discussion. Although the themes were previously chosen for each meeting, the group will be conducted according to women necessity and other themes can arise.

The final interviews among focus groups and questionnaires will be performed by a researcher that did not participate in the group.

### Sample size

The sample size determined was 12–15 participants per group, taking into account sample size recommendations for pilot studies [21,22]. The sample will consider new cases attended at the research setting in each period. Fig illustrates the process in SPIRIT flowchart [Fig 1].

**Fig 1 pone.0326084.g001:**
[figure not shown]
SPIRIT flowchart.

### Statistical analysis

The quantitative data will be saved in a spreadsheet of Microsoft Excel® Software and will be stored for a five-year period. A descriptive analysis will be conducted using measures of central tendency and dispersion for quantitative variables and frequencies and percentages for categorical variables. The groups and time periods will be compared with regard to quantitative outcomes using the unpaired or paired Student’s t-test, Mann-Whitney test or paired Wilcoxon test, according to the data distribution.

Data distribution will be assessed using the Shapiro-Wilk test. Pearson’s chi-square, Fisher’s exact or McNemar’s tests will be used for categorical outcomes. The Bonferroni correction [23] will be applied to the significance level according to the number of comparisons made for each outcome variable. The significance level was set at 5% and the program *Statistical Analysis System* (SAS), version 9.4 will be used.

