### Randomization and masking method

After accepting to participate in the research and signing the informed consent form, the researcher will randomly select the assigned group. We will use a computerized randomizer. A random sequence will be generated by a computer software (http://www.random.org/) and will be followed for the allocation of participants into the experimental and control groups. A sealed envelope containing the randomization form previously filled out in the Intervention Group or Control Group, which will be opened and read with the patient.

The study will not be masked, since the pregnant woman and the researcher will know whether the patient belongs to the IG or CG.The Intervention Group (IG) is going to be composed by a maximum of 15 pregnant women. The group will be attending in 11 meetings with approximately two-hour duration each, every 4 weeks or earlier, if necessary, with the following themes discussions:

Nutrition and physical activity during pregnancy; Most common management complaints and signs of complications; Social and social security rights and mental health; Reproductive planning and sexuality; Childbirth preparation guidelines, warning signs and maternity visit; Breastfeeding; Gestational complications and preparation for trousseau; Cognitive and physical development of the child; Nutrition in the fourth quarter; Postpartum follow-up routines and group closure.

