### Follow-up

The pregnant women will be followed during all pregnancy period (with one postpartum review) through scheduled visits in every 4 weeks or earlier (according to women necessity), with a minimum of 10 group consultations. The women can come to the hospital other days for laboratory exams, but the attending will always happen in the group.

At each meeting, for each participant, the meeting information will be recorded on an antenatal card, with information like: attendance data, meeting number, gestational age, weight, blood pressure, uterine height, fetal heart rate, fetal movements, fetal presentation, edema, time to return to the clinic, local and professional care. The Control Group (CG) will follow individualized antenatal care according to the service routine, which consists of medical and nursing visits scheduled every 4 weeks or earlier, if necessary.

The data collection process will occur during all antenatal care period. After the inclusion in the research and before starting the antenatal care, the participants (from both groups) will answer a questionnaire about social and demographic questions. Then, will participate in a semi direct individual interview with themes related to women’s expectations about antenatal care and will answer, individually, World Health Organization Quality of Life (WHOQOL brief) [18], State-Trait Anxiety Inventory (IDATE) [19] and Edinburgh [20] scale questionnaires.

Women allocated in intervention group, will participate in focus group also with themes related to women’s expectations about antenatal care, at the first attending of group antenatal care. To evaluate the intervention’s effectiveness, at the finals attending of antenatal care (preferably after 38 weeks of pregnancy) or in postpartum visit, all pregnant women included in the study will answer again the WHOQOL, IDATE and Edinburgh scale questionnaires and a new individual interview will be performed. In all intervention group meetings, pre and post-tests will be carried out on the experience and satisfaction regarding the central theme of each meeting. A new focus group will be performed with both groups (intervention and control).

Women who withdraw or have a medical recommendation to leave IG will be discontinued and these will also participate in an interview with open questions to assess the reasons for giving up on group antenatal care.

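### Unadjusted between-arm tests and within-arm pre-post tests share one per-outcome Bonferroni divisor; one baseline-adjusted comparison per questionnaire score would be clearer and usually more precise

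*Protocol article*

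**What the plan says.** - **Tests.** In the Statistical analysis section: "The groups and time periods will be compared with regard to quantitative outcomes using the unpaired or paired" t-test, the Mann-Whitney test or the paired Wilcoxon test, depending on the distribution. No covariate, change-score contrast or group-by-time term is named.
- **Significance level.** It is 5%, and "The Bonferroni correction [23] will be applied to the significance level according to the number of comparisons made for each outcome variable". The number of comparisons is not given.
- **Measurements.** In the Follow-up section, women in both arms "will answer, individually, World Health Organization Quality of Life (WHOQOL brief) [18], State-Trait Anxiety Inventory (IDATE) [19] and Edinburgh [20] scale questionnaires" before care starts. At the last antenatal visits or the postpartum visit, all of them "will answer again the WHOQOL, IDATE and Edinburgh scale questionnaires". That section gives evaluation of effectiveness as the purpose of the second measurement.
- **Size.** "The sample size determined was 12–15 participants per group, taking into account sample size recommendations for pilot studies". No power target, effect size or SD is stated. The intervention arm "is going to be composed by a maximum of 15 pregnant women".
- **Aim.** The Background section lists a comparison of outcomes between the two care models. The Discussion section expects better quality of life, anxiety and depression results with group care than in the control group.

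**The concern.** The question put to the questionnaire scores is whether the randomised arms differ. A paired test within one arm does not answer it: it measures change over time from any cause. If one arm crosses the significance threshold and the other does not, this is easily read as an effect of group care even when the arms do not differ.

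The within-arm tests also count as comparisons for the same outcome. Under the stated Bonferroni rule they therefore lower the alpha left for the between-arm test. Finally, each woman has a baseline value of each score, but no stated between-arm test uses it as a covariate, so its predictive information does not sharpen the estimate. With 12 to 15 women per arm there is little precision to spare.

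**Working it through.** **The plan's own figure.** The 12–15 per group cannot be reproduced as a power calculation, because it rests on pilot-study recommendations. What follows compares two analyses at that size.

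**Inputs.** From the protocol article: n = 12 or 15 per arm and a 5% level divided by K. Assumed, because not stated: two-sided tests, no dropout, standardised effect d = 0.8, K = 1, 2 or 4, and baseline-to-end correlation ρ from 0 to 0.7. K = 2 would be one between-arm and one time comparison. K = 4 would be two between-arm tests (baseline and end) and two within-arm tests.

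**Step 1: how often within-arm tests disagree when the arms do not differ.** Assume both arms shift by 0.5 SD and ρ = 0.5. The SD of the change is √[2(1 − 0.5)] = 1, so the noncentrality is 0.5√n, which is 1.73 (n = 12) or 1.94 (n = 15), with n − 1 degrees of freedom. With p the chance that one arm is significant, exactly one of two arms is significant with probability 2p(1 − p).

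| n per arm | alpha | p | exactly one arm significant |
|---|---|---|---|
| 12 | 0.05 | 0.353 | 46% |
| 15 | 0.05 | 0.438 | 49% |
| 12 | 0.0125 | 0.158 | 27% |
| 15 | 0.0125 | 0.220 | 34% |

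**Step 2: planned unpaired t-test of end scores.** Noncentrality = d√(n/2), with 2n − 2 degrees of freedom and level 0.05/K. For n = 15 it is 0.8 × √7.5 = 2.19; for n = 12 it is 0.8 × √6 = 1.96.

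**Step 3: one ANCOVA at 5%.** Noncentrality = d√(n/2) / √[(1 − ρ²)(1 + 1/(2n − 5))], with 2n − 3 degrees of freedom. The last factor is the small-sample price of estimating the covariate slope. For n = 15 and ρ = 0.5: 2.19/√(0.75 × 1.04) = 2.48, which gives 66.7%.

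| Power at d = 0.8 | n = 12 | n = 15 |
|---|---|---|
| t-test, K = 1 | 46.6% | 56.2% |
| t-test, K = 2 | 34.7% | 44.1% |
| t-test, K = 4 | 25.0% | 33.4% |
| ANCOVA, ρ = 0 | 44.5% | 54.4% |
| ANCOVA, ρ = 0.3 | 48.0% | 58.4% |
| ANCOVA, ρ = 0.5 | 55.7% | 66.7% |
| ANCOVA, ρ = 0.7 | 72.3% | 82.6% |

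Simulation with 20,000 trials per cell agreed within about one percentage point.

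**Step 4: where the gain comes from (n = 15).**
- Removing the divisor alone adds 56.2 − 44.1 = 12.1 points if K = 2, and 56.2 − 33.4 = 22.8 points if K = 4.
- Adjusting for baseline alone adds 54.4 − 56.2 = −1.8 points at ρ = 0, +2.2 at ρ = 0.3, +10.5 at ρ = 0.5 and +26.4 at ρ = 0.7.

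**The case against.** The strongest reply is that this is a pilot with no power target, that an unadjusted comparison of randomised arms is valid, and that its confidence interval already allows for chance imbalance. Covariate adjustment may also be set out in an analysis plan that is not shown. The first part stands: the planned between-arm test is not wrong, and power is not the main yardstick for a pilot. But the article does fix significance tests and a Bonferroni rule, and a pilot is served best by one clear estimate of the difference between arms.

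The correlation may also be low. Baseline is before 20 weeks and the end measurement is preferably after 38 weeks or postpartum, so the two lie months apart. This stands too: at a correlation of about 0.2 adjustment gains nothing, and at 0 it costs about 2 points.

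Several stronger readings are tempting, but the documents do not support them:
- **That baseline scores will be tested between arms, with four comparisons per outcome.** The text says neither; K = 4 is only one possible reading.
- **That the baseline scores are wasted.** The paired tests use them, and the article does not say whether the unpaired test is on end scores or on changes. If it is on changes, simulated power at 5% and n = 15 is about 43%, 56% and 77% for correlations 0.3, 0.5 and 0.7, still below ANCOVA.
- **That choosing the test by Shapiro-Wilk does damage.** A simulation of that two-stage procedure at these sizes gave type I error of 4.9–6.1% at a nominal 5%, so no material harm is shown.
- **That error across outcomes is inflated by a known amount.** This would need a count of outcomes and an assumption that they are independent. The article gives no such count, and scores from the same women are unlikely to be independent.
- **That pregnancy itself moves these scores in both arms.** No passage says so; the equal shift in Step 1 is an assumption.

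**Conclusion.** The point holds as a near-costless improvement to the analysis of the questionnaire scores, not as an error that invalidates the trial. Two parts rest on the text itself: within-arm tests stand beside between-arm tests without being an estimate of the randomised effect, and under the Bonferroni rule they take alpha from the comparison that is.

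The size of the loss rests on assumed K, correlation and effect size. For d = 0.8 and K of at least 2, changing both features gains about 10 points of power even at zero correlation (44.1% to 54.4% at 15 per arm; 34.7% to 44.5% at 12). It gains more as the correlation or K rises. If K is 1, the gain depends on the correlation alone and can be slightly negative. Even the better analysis exceeds 80% power in only one of the cases examined (15 per arm, correlation 0.7). The main benefit is therefore an interpretable estimate with its interval.

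**What to change.** For each WHOQOL, IDATE and Edinburgh score, state one between-arm comparison: ANCOVA of the final score on arm plus the baseline value of that score, reported as an adjusted mean difference with 95% CI. Present within-arm changes descriptively, without tests, and say that they do not count towards the Bonferroni divisor.

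The cost is one degree of freedom per model and a change to the wording of the Statistical analysis section. No further data are needed, since both measurements are already planned in both arms. The change should be recorded before the end scores are examined.

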### Qualitative analysis

The qualitative data from individual interviews and focus group will be recorded and transcribed, then anonymous encoded and will be storage in two ways: At NVIVO14 Software and in the research pen drive, for a five-year period. Qualitative data will be analyzed by themes in the following steps: 1) Text edition to transcription maintained the originals traits of participants; 2) Listen and rereading of transcriptions; 3) Comments and registered impressions in front of this rereading, writing at right bank of transcribed text; 4) Categorization and subcategorization of information; 5) Presentation and discussion of material to pairs; 6) Categories definition as result of material enhancement and data validation by pairs [24] .

All material used for data collection will be stored in two ways: on the NVIVO 14 software platform and in the UNICAMP data repository (REDU- https://www.sbu.unicamp.br/sbu/repositorio-de-dados-de-pesquisa-da-unicamp/). This article has followed the SPIRIT guidelines for its elaboration [25] [S1 File].

### Plan for translation and dissemination of scientific knowledge

During the IG meetings, materials (leaflets with QR codes) will be distributed to popularize scientific knowledge on the various topics covered, enabling access and sharing of the topics discussed at any time. This way, women will be able to review information, reflect and formulate questions for the next meetings, share and talk with family members and support networks in general. Professionals working in CAISM’s antenatal care clinics will be informed about the results of the intervention at the end of the implementation of the pilot project, and dissemination to the scientific community will be done through the production and publication of scientific articles.

### Quality control

Procedures will be adopted for quality control, such as: subject identification numbers to prevent data loss or confusion; review of completed forms, organization of instruments, and verification of the coding of textual responses; data will be entered into the database by two different data entry clerks to avoid data loss or typing errors.

### Reports the status and timeline of the study

A) initial training for the intervention team will be held in March and June 2025; B) participant recruitment has not started and is scheduled to take place between May 01 and June 30, 2025; C) data collection will be completed by January, 2026; D) Qualitative data analysis and validation with peer researchers, using NVIVO14 and Quantitative analysis with support from the university’s statistics service and E) results are expected by March, 2026.

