### Inclusion and exclusion criteria

The inclusion criteria are pregnant women with 18 years old or more; gestational age (GA) less than 20 weeks of gestation and antenatal care at the study setting. - The exclusion criteria is professional indication validated by a professor to individualize care (will be sent to the indicated professionals or sectors, e.g., hospitalization, another outpatient clinic, etc.).

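### The January 2026 close of data collection does not follow from the plan's own recruitment window, meeting schedule and postpartum review

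*Protocol article*

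**What the plan says.** The calendar is in the protocol article, *Reports the status and timeline of the study*: "participant recruitment has not started and is scheduled to take place between May 01 and June 30, 2025", then "data collection will be completed by January, 2026", and "results are expected by March, 2026".

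The quantities that should produce those dates are elsewhere in the article:

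- *Inclusion and exclusion criteria* admits women at "gestational age (GA) less than 20 weeks of gestation", with no lower limit.
- *Randomization and masking method* sets the intervention at "11 meetings with approximately two-hour duration each, every 4 weeks or earlier, if necessary".
- *Follow-up* covers the whole pregnancy and one postpartum review, "with a minimum of 10 group consultations". It puts pre- and post-tests at every intervention meeting. The closing WHOQOL, IDATE and Edinburgh scales are due at the last antenatal visits, ideally beyond 38 weeks, or at the postpartum visit. Maternal and perinatal outcomes come from the medical records.

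**The concern.** A closing date should be the entry date of the slowest participant plus the time her follow-up needs. Here it appears to have been set independently: the meetings alone take longer than the calendar allows, before any postpartum review is added. If the date is applied as written, whatever falls after it is not collected. The women affected are those who enter both late in the window and early in pregnancy. With 12 to 15 women per group, losing a handful of postpartum reviews matters.

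A second conflict does not depend on the calendar. The number of meetings, the minimum, the nominal interval and the gestational-age limit cannot all hold for most of the eligible range. Implementing the group model is the first aim of this pilot, so the planned amount of intervention needs to be coherent.

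**Working it through.** **Inputs from the article.** Entry 1 May to 30 June 2025; close in January 2026, read generously as 31 January; 11 meetings, minimum 10; nominal interval 4 weeks; entry below 20 weeks.

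**Assumptions, not in the article.** First meeting on the day of entry, which is the earliest possible and so favours the plan; birth at 40 weeks; postpartum visit 4 or 6 weeks after birth.

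**1. Time available.** 1 May to 31 January is 275 days, or 275/7 = 39.3 weeks. 31 May to 31 January is 245 days, or 35.0 weeks. 30 June to 31 January is 215 days, or 30.7 weeks.

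**2. Time the meetings need.** Span = (meetings − 1) × 4 weeks.

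- Eleven meetings: 10 × 4 = 40 weeks. The last falls on 5 February 2026 (1 May start) to 6 April 2026 (30 June start). The latest start that would fit is 31 January less 40 weeks, or 26 April 2025, before recruitment opens.
- Ten meetings: 9 × 4 = 36 weeks. They fit only if the first is by 24 May 2025.
- Mean spacing that would fit eleven: 39.3/10 = 3.93 weeks from 1 May, and 30.7/10 = 3.07 weeks from 30 June.

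The January 2026 date is therefore not reproduced at the nominal interval for any entrant.

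**3. Follow-up milestones.** Lowest gestational age at entry that reaches a milestone by 31 January = milestone − weeks available.

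| Entry | 38 weeks | Birth (40) | Postpartum visit at 4 weeks (44) | Postpartum visit at 6 weeks (46) |
|---|---|---|---|---|
| 1 May | all | 0.7 | 4.7 | 6.7 |
| 31 May | 3.0 | 5.0 | 9.0 | 11.0 |
| 30 June | 7.3 | 9.3 | 13.3 | 15.3 |

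**4. Illustrative share cut off.** The article gives no distribution of gestational age at entry, so two are assumed, each with entry uniform over the window.

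| Gestational age at entry | 38 weeks missed | Birth missed | Postpartum visit missed (4 to 6 weeks) |
|---|---|---|---|
| Uniform 6 to 20 weeks | 0.8% | 4.6% | 22% to 36% |
| Uniform 10 to 20 weeks | 0% | 0% | 6.5% to 16.5% |

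In 24 to 30 women, the postpartum column is about 5 to 11 women (0.22 × 24 to 0.36 × 30) in the first row and about 2 to 5 (0.065 × 24 to 0.165 × 30) in the second. Birth after the close is about one woman (0.046 × 24 to 30 = 1.1 to 1.4) or none. Missing 38 weeks is well under one woman (0.008 × 30 = 0.24).

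**5. Meeting count against gestation.** Meetings by 40 weeks at the nominal interval = floor((40 − gestational age)/4) + 1. This gives 6 for entry just under 20 weeks, 7 at 16, 8 at 12 and 9 at 8. With the one postpartum review added, ten is reached only by entry at 8 weeks or earlier. Nine antenatal meetings by 40 weeks mean eight intervals, so the spacing would have to be (40 − 12)/8 = 3.5 weeks from 12 weeks, 3.0 from 16, and about 2.5 from just under 20.

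**The case against.** The best defence is that four weeks is not a fixed interval: the article allows closer visits where needed. A reader might infer that no woman can complete 11 meetings, or that the planned intervention is unreachable. The documents do not support that. Eleven meetings fit before the close at mean spacings of 3.93 to 3.07 weeks. What stands is that closer spacing is described as depending on need, whereas meeting the stated counts would make it routine, and the article does not say so.

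A reader might also infer that the final WHOQOL, IDATE and Edinburgh scores are cut off. They largely are not. The postpartum visit is one of two permitted occasions and 38 weeks is a preference. Only women who enter at the very end of June and below about 7.3 weeks miss that point. Very early entry is also less likely here: *Setting* describes referral from primary care, and *Potential limitations and mitigation strategies* anticipates late initiation of care.

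Nor is everyone who enters late, or everyone who enters early in pregnancy, affected. A 30 June entrant at 16 weeks has even a 6-week postpartum visit on 26 January 2026, and a 1 May entrant at 8 weeks has hers on 22 January. It is the combination of late entry and early gestation that causes the loss.

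Two further inferences fail. Entry date and gestational age are fixed before allocation, so the cut-off by itself does not bias the comparison between arms. And no section defines adherence as attendance out of 10 or 11, so the plan does not build in a failed adherence result.

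**Conclusion.** The concern holds in a limited form. The closing date contradicts the recruitment window, the nominal meeting schedule and the postpartum review. The meeting result needs only the article's own figures, a first meeting no earlier than entry, and the nominal interval. The postpartum thresholds (13.3 to 15.3 weeks for 30 June entrants, 9 to 11 weeks for 31 May entrants) also rest on the assumed birth at 40 weeks and visit 4 to 6 weeks later. The number of women affected rests further on an assumed spread of gestational age at entry.

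The data at risk are postpartum reviews, the last group meetings with their pre- and post-tests, and perinatal records for a few women who enter both late and early in gestation. Separately, the minimum of 10 consultations is not met at the nominal interval by women entering after 8 weeks, which is most of the eligible range. This is a moderate point: the contradiction is clear, the loss is partial, and the repair is cheap.

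**What to change.** In *Reports the status and timeline of the study*, define the end of data collection as the last postpartum visit of any participant. Naming the last woman randomised would not be enough. Under the same assumptions, a woman randomised on 20 June at 7 weeks reaches 40 weeks on 6 February 2026, while one randomised on 30 June at 18 weeks does so on 1 December 2025.

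For a 30 June entrant at 6 to 8 weeks (assumed), the last visit falls between 9 March 2026 (30 June + 44 − 8 = 36 weeks) and 6 April 2026 (30 June + 46 − 6 = 40 weeks). The March 2026 results date must move accordingly. State when the postpartum review is due, so that the closing date can be derived.

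The authors must also reconcile the number of meetings, the minimum of 10, the four-week interval and the entry limit across *Inclusion and exclusion criteria*, *Randomization and masking method* and *Follow-up*. Which of these should change is for them to decide. If attendance is reported, express it for each woman as meetings attended over meetings possible given her entry.

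The cost is a close 37 to 65 days after 31 January, about 5 to 9 weeks, plus wording changes. No extra participants are needed.
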